## ESCAPE trial: Statistical Analysis Plan

### 1. Objectives of the study

To determine if endovascular mechanical thrombectomy is superior to best standard of care in an imaging-selected population of acute ischemic stroke patients.

### 2. Study Design

Prospective, randomized, open-label with blinded outcome evaluation (PROBE) design.

### 3. Sample size

There is now empirical evidence that the mRS scale, when categories 5 and 6 are combined, is a truly interval scale meaning that the difference in utility (or function) between any one step increment in the scale is the same; thus, it is unlikely that the proportional odds assumption will be violated. The trial is powered to detect a statistically significant shift in the distribution of scores on the mRS scale at 3 months between the treatment and the control arm, assuming that categories 5 and 6 (bedbound with severe disability, and death) are collapsed into one category, and the effect leads to an assumed common odds ratio of 1.8. The expected distribution of outcomes is based upon the pooled experience from the literature [SWIFT study, STAR registry, Calgary data, IMS-3 study limited to an ESCAPE population, ALIAS part 1 study limited to an ESCAPE population] and a 5% increase in favourable outcome per mRS category. [Figure 1] In IMS-3 there was an average 2% non-significant improvement in favourable outcomes per mRS category; in SWIFT (which compared two endovascular devices), there was an average 8% improvement in favourable outcomes per mRS category. Using Calgary data, the common OR for improvement across the mRS scale with endovascular treatment compared to IV only was 2.1 (CT95 1.1-4.2). [[name], unpublished data]

A total sample size of 188 patients per group is required for 90% power, two-sided alpha at 0.05 and 1:1 randomization to detect a common OR of 1.8, based upon the expected distribution shown below (figure 1). The sample size calculation is based upon Whitehead's power formula. The sample size is estimated without knowing the distribution of pre-specified confounding variables. We assume no cross-overs. Allowing for losses-to-follow-up (of up to 6%, n=24/400), a total required sample size of 400 ideal patients is anticipated. However, we know that the effect size is highly dependent upon very rapid treatment times and have planned to continue enrolling patients until up to 200 endovascular patients have been treated with a CT-to-first reperfusion time < 90 minutes. Currently, in our initial patients we are meeting this quality metric in 60% of our patient population, compared to our desired 80% or greater. We conservatively assume that the effect size is absent if we do not achieve our target treatment times. Therefore,

(1) the trial is powered to detect an effect size based upon 400 ideal patients

(2) the maximum sample size for the trial will be 500 patients to ensure that 200 patients in the endovascular group meet the target treatment times (i.e. are ideal patients).

Figure 1. Projected outcomes by mRS category

[figure not shown]

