## 8. Missing data

Under the ITT principle, all patients who are randomized are included in the analysis. Therefore, missing data, especially in the outcome measures, can be problematic. Thus every effort will be made to keep all missing data to a minimum. In the event that, despite the clinical centers' best efforts, there are missing data, then for the primary outcome analysis, missing outcome data will be imputed by assuming the missing mRS score at 3 months to be unfavorable. We will assign the worst possible score. If the patient is known to be alive, we will impute a score of 5. If the patient is not known to be alive or dead, we will impute a score of 6.

Furthermore, if the assessment was conducted outside of the protocol-specified time window, data obtained are still included in the analysis, with the rationale that it is a more accurate measure than those obtained by imputation. At a minimum 90-day outcome assessments will be accepted within a +/- 30-day window.

For sensitivity analysis, the missing outcome values will be imputed using the following methods:

- If one-month or 5-day/discharge outcome scores are available, carry forward those values; else, assume the worst case.
- Assign failure (worst possible score) to all subjects with missing 3-month outcome data.
- Multiple imputation method based on the regression model
- Hot-deck or nearest neighbor method, using clinical site, age, sex, baseline NIHSS, baseline serum glucose, baseline ASPECTS, IV tPA use, treatment group as classification variables.
- Regression method, with age, sex, baseline NIHSS, baseline serum glucose, IV tPA vs. non-IV tPA, and treatment group as covariates.
- In the endovascular group, impute values for LTFU with failure (worst possible score), and in the control group, with success (the best-worst case imputation) in the intervention group.

Similar imputation methods will be employed for secondary categorical outcomes. For the raw NIHSS score, multiple imputation, regression, and mean substitution methods will be used in the sensitivity analyses. Missing covariate data, if any, will be imputed using either multiple imputation or regression method, if needed.

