## 9. Efficacy Analysis

### 9.1. Primary analysis

The primary analysis will be conducted on an intention-to-treat basis using a proportional odds model (ordinal logistic regression) with an assumed common odds ratio of improvement on the mRS. We will test whether the proportional odds assumption is satisfied using chi square test. A secondary analysis will use an additive multivariable model adjusting for all the minimization variables included as co-variables. Only main effects will therefore be considered in this model. The results will be expressed as an odds ratio with 95% confidence limits. Additional analyses will include a safety population analysis defined to include only those patients who

received an interventional procedure, an on-protocol analysis including those patients who were treated according to protocol. If the proportional odds assumption is not satisfied we will revert to a binary outcome of independence (mRS 0-2) vs. dependence or death (mRS 3-6) at 90 days. This will be assessed using a Fisher's exact test.

The primary analysis will be unadjusted. Because the randomization is being balanced a priori according to key prognostic variables (age, sex, NIHSS, ASPECTS, occlusion location and tPA use), we expect that the unadjusted analysis will be similar to the adjusted analysis.

A revised statistical analysis plan may be modified according to the statistical distribution of variables and finalized prior to breaking the blind.

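### The 90% power in SAP Section 3 is for 400 patients who all meet the time target; on the plan's own assumption, the intention-to-treat primary analysis has about 82-83% at 80% attainment and 58-59% at 60%, and the 500 cap does not guarantee 200 ideal patients

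*SAP*

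**What the plan says.** Section 3 of the SAP sets the effect and the size: "the effect leads to an assumed common odds ratio of 1.8", and "A total sample size of 188 patients per group is required for 90% power, two-sided alpha at 0.05 and 1:1 randomization". A 6% loss allowance takes the 376 to 400, described as ideal patients.

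The section then turns to treatment delay. The target is a CT-to-first-reperfusion time under 90 minutes. The plan reports that "in our initial patients we are meeting this quality metric in 60% of our patient population", against a desired 80% or greater, and adds: "We conservatively assume that the effect size is absent if we do not achieve our target treatment times". Two conclusions follow. Power is based on 400 ideal patients, and the "maximum sample size for the trial will be 500 patients to ensure that 200 patients in the endovascular group meet the target treatment times".

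Section 5.1 defines the efficacy population as all randomized patients by intention to treat. Section 9.1 agrees: "The primary analysis will be conducted on an intention-to-treat basis", with an unadjusted proportional odds model. Section 8 keeps patients with no 3-month outcome in that analysis: "missing outcome data will be imputed by assuming the missing mRS score at 3 months to be unfavorable".

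**The concern.** The population that is powered is not the population that is analysed. Section 3 computes power as if every endovascular patient were treated in time. Section 9.1 compares all randomized patients, including endovascular patients for whom Section 3 assumes no effect. No primary analysis is limited to ideal patients. Nor could one easily be: attainment is known only after randomization, and controls have no counterpart to it.

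The step from 400 to 500 is offered as the remedy for late treatment, but the extra patients come with the late-treated ones still in the comparison. The plan gives no power for that diluted comparison, and its cap cannot guarantee 200 ideal patients at the attainment rate it reports. The loss allowance has a similar mismatch: Section 3 treats lost patients as removed, whereas Section 8 gives them the worst score in both arms.

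What is at stake is how a neutral result would be read. It would be set against a stated 90% that the planned test does not have under the plan's own premises.

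**Working it through.** **Inputs.** From Section 3: common odds ratio 1.8, two-sided alpha 0.05, 90% power, 1:1 allocation, Whitehead's formula, six categories (mRS 5 and 6 combined), 6% loss, zero effect if late, attainment 60% now and 80% or greater desired, stop at up to 200 ideal endovascular patients, cap 500. Assumed: the outcome distribution, because Figure 1 is not shown. I use six equal pooled categories, for which 1 − Σp³ = 1 − 6(1/6)³ = 0.9722, and check against four uneven distributions.

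**1. The plan's own figure.** With ln 1.8 = 0.5878:

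n per arm = 6(1.960 + 1.282)² / [(0.5878)² × 0.9722] = 6 × 10.507 / (0.3455 × 0.9722) = 187.7, so 188.

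The uneven distributions give 187.9 to 190.5. Then 376/0.94 = 400. Both stated figures reproduce.

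**2. Where 500 comes from.** 2 × 200/0.80 = 500. The cap is the head count needed for 200 ideal endovascular patients on average at exactly 80% attainment.

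**3. Dilution.** If a fraction f of the endovascular arm has odds ratio 1.8 and the rest has 1.0, the average log odds ratio is close to f × ln 1.8:

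- f = 0.80: 0.4702, odds ratio 1.60
- f = 0.60: 0.3527, odds ratio 1.42

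Information is proportional to N × (log odds ratio)². Relative to 400 ideal patients, 500 patients give 1.25 × 0.80² = 0.80 of the information at 80% attainment and 1.25 × 0.60² = 0.45 at 60%.

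**4. Intention-to-treat power, 6% dropped.** Power = Φ(√(n × 0.9722/6) × f × 0.5878 − 1.960), with n evaluable per arm:

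| Attainment | Enrolled per arm | n | Calculation | Power |
|---|---|---|---|---|
| 100% | 200 | 188 | Φ(3.244 − 1.960) | 90.0% |
| 90% | 222.2 (stop at 200 ideal) | 208.9 | Φ(3.078 − 1.960) | 86.8% |
| 85% | 235.3 (stop at 200 ideal) | 221.2 | Φ(2.991 − 1.960) | 84.9% |
| 80% | 250 (cap) | 235 | Φ(2.902 − 1.960) | 82.7% |
| 60% | 250 (cap) | 235 | Φ(2.176 − 1.960) | 58.6% |

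A second calculation builds the endovascular distribution as a mixture, f × shifted + (1 − f) × control, and fits the proportional odds model to the expected data. Across the four uneven distributions it gives 81.9% to 82.4% at 80% and 57.6% to 58.0% at 60%.

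**5. Lost patients given the worst score (Section 8).** With 6% in each arm placed in the combined worst category and all enrolled patients kept, the same mixture method gives:

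| Design | Odds ratio | Power |
|---|---|---|
| 400, all ideal | 1.71 to 1.73 | about 86% (86.2% to 86.6%) |
| 500, 80% ideal | 1.54 to 1.55 | about 78% (77.7% to 78.2%) |
| 500, 60% ideal | 1.38 to 1.39 | about 53% (53.1% to 53.7%) |

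**6. Does the cap deliver 200 ideal patients?** Of 250 endovascular patients, 250 × 0.60 = 150 are expected to be ideal at 60%, and 250 × 0.80 = 200 at 80%. The exact binomial chance of at least 200 is 54% at 80% and effectively zero at 60%. At 60%, 200 ideal patients would need 2 × 200/0.60 = 667 in total.

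**The case against.** The strongest defence is that the plan is open about its basis. It says that power refers to 400 ideal patients, discloses the 60% rate, and calls zero late effect conservative. It speaks of a maximum and of up to 200 patients, and no stated arithmetic is wrong. No test, estimate or analysis set is affected, and the result will be reported as an odds ratio with 95% limits, which itself shows what a neutral result excludes.

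Much of this stands, and it rules out several stronger readings:

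- A reader might infer that the 188 is wrong. It is not; it reproduces.
- A reader might take 83% as a ceiling. The plan aims for 80% or greater. Stopping at 200 ideal patients, power is about 85% at 85% attainment and 87% at 90%. With no losses it is about 85% at 80% attainment.
- A reader might take 59% as the trial's actual power. It requires both that attainment stays at the rate seen in the initial patients and that late treatment has exactly no effect. Any partial late benefit raises it.
- A reader might apply the final boundary of 2.004 from Section 4, which would lower the dropped-loss figures to about 81-82% and 56-57%. Section 4 derives that boundary for the binary outcome, and the SAP does not clearly say that it governs the ordinal test.

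The defence does not answer the main point. Section 3 presents the cap as the consequence of its no-effect assumption and as securing 200 ideal patients, yet never carries that assumption into the intention-to-treat test on which the trial will be judged.

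**Conclusion.** The point holds as a mismatch between the powered and the analysed population. Under the plan's own assumption of no effect in late-treated patients, and with its 6% loss allowance, raising enrolment to 500 does not restore 90% power at any attainment the plan contemplates short of 100%. With 500 enrolled, power is about 82-83% at the 80% target and 58-59% at the reported 60% with losses dropped, or about 77-78% and 53% with losses scored worst. On the worst-score basis even 400 all-ideal patients give about 86%. The claim that the cap secures 200 ideal patients fails at 60% (150 expected) and is close to an even chance at exactly 80%.

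The figures rest on an assumed mRS distribution, which moves power by less than 1 point across the uneven distributions tried; on losses of 6% in each arm; and on zero late effect, which is a conservative bound. The documents do not support saying that enrolment must change.

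**What to change.** Restate Section 3 for the intention-to-treat comparison, on one loss-handling basis, preferably the worst-score rule of Section 8. The sponsor should recompute the figures from its own Figure 1 distribution. Suggested content:

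> The 90% power refers to 400 patients who all meet the 90-minute target, with patients lost to follow-up dropped. For the intention-to-treat primary analysis with 500 enrolled, 6% lost and scored worst, and no effect in patients who miss the target, power is about 77-78% if 80% meet the target and about 53% if 60% do. Zero effect in late-treated patients is a conservative bound.

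If the sponsor keeps the dropped-loss basis instead, the corresponding figures are about 82-83% and 58-59%; the two bases should not be mixed. Replace the statement that the cap ensures 200 ideal endovascular patients with the expected numbers: about 150 at 60% attainment and 200 on average at 80%.

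The cost is SAP wording and one recalculation. Enrolment, the cap and the analysis stay as they are; the stated power becomes less favourable.

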#### 4. Interim Analyses

We will plan for two interim analyses after 125 and 300 patients have completed 3-month follow-up. At the safety analyses (n=125) the DSMB will be asked to consider safety only. The second analysis (n=300) will assess for safety and overwhelming efficacy and make recommendations accordingly. We will use O'Brien-Fleming boundaries at the interim analysis as follows:

There are no established techniques for the assessment of interim trial efficacy boundaries using an ordinal logistic regression model (proportional odds model). Instead, we will revert to a simple dichotomous analysis of the mRS score at 0-2 defined at 90 days from randomization. [This approach is also being used in other interventional treatment trials in stroke.] The Z-statistic for this analysis shall be derived from the normal approximation of the binomial distribution as an unadjusted two-sample test of proportions.

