#### *O'Brien Fleming Boundary for a Binary Primary Endpoint*

*For a RCT comparing two treatment arms with respect to a binary outcome and one interim analysis, the binary test statistic is given as*

$$Z_k = \frac{(p_{Ak} - p_{Bk})}{\left\{ \sqrt{\bar{p}_k(1 - \bar{p}_k) / \left( \frac{1}{n_A} + \frac{1}{n_B} \right)} \right\}}, k = 1, \dots, K = 2$$

where  $\bar{p}_k = \frac{p_{Ak} + p_{Bk}}{2}$ , where  $P_{Ak}$  and  $P_{Bk}$  are the estimated proportions in treatment arms A and B at stage k, respectively. The two-sided sequential test based on O'Brien & Fleming boundary is given as

1. At stage 1 (interim analysis, n=300): Reject  $H_0$  and stop the trial at stage k if:  
 $|Z_k| \geq C_B(2_{z0.05})\sqrt{2} = 2.834$

Else if  $|Z_k| < C_B(2_z 0.05)\sqrt{2} = 2.834$ , continue to stage 2.

2. At stage 2 (final analysis): Reject  $H_0$  at stage  $k$  if:  $|Z_k| \geq C_B(2_z 0.05) = 2.004$

Therefore, for a RCT with one interim analysis and a final analysis (i.e.,  $K = 2$ ), the critical boundaries at Stage 1 and Stage 2 (final analyses) are 2.834 and 2.004, respectively.

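### The efficacy look uses a binary mRS 0-2 test on the incorrect ground that ordinal boundaries do not exist, and no critical value is assigned to the final ordinal test

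*SAP*

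**What the plan says.** - **Timing (section 4).** There are two looks. The one at n=125 is for safety only. Of the other: "The second analysis (n=300) will assess for safety and overwhelming efficacy and make recommendations accordingly".
- **Interim statistic (section 4).** The plan first asserts: "There are no established techniques for the assessment of interim trial efficacy boundaries using an ordinal logistic regression model (proportional odds model"). It then says: "Instead, we will revert to a simple dichotomous analysis of the mRS score at 0-2 defined at 90 days from randomization". The Z is "derived from the normal approximation of the binomial distribution as an unadjusted two-sample test of proportions". A bracketed remark adds that other stroke trials do the same.
- **Boundaries (section 4, O'Brien-Fleming subsection).** The subsection is headed for a binary primary endpoint and opens: "For a RCT comparing two treatment arms with respect to a binary outcome and one interim analysis, the binary test statistic is given as". It concludes that "the critical boundaries at Stage 1 and Stage 2 (final analyses) are 2.834 and 2.004, respectively". The stage 2 rule, which begins "At stage 2 (final analysis): Reject", applies to that same binary Z.
- **DSMB guidance (section 4).** If the binary Z exceeds 2.834, the committee turns to the ordinal model, then mortality, then the two tPA subgroups, and uses its judgment. No boundary is given for the ordinal result.
- **Final analysis (section 9.1).** The primary analysis is an unadjusted proportional odds model. If proportional odds fails, mRS 0-2 is compared by Fisher's exact test. On reporting: "The results will be expressed as an odds ratio with 95% confidence limits". No critical value is stated.

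**The concern.** The interim statistic and the decisive final statistic differ, and the reason given for the difference is wrong. As a result, 2.004 belongs to a test that section 9.1 never performs: the primary test is ordinal, and the binary fallback is Fisher's exact test rather than the two-sample Z. Since 2.004 corresponds to a two-sided p of 0.045, an ordinal p between 0.045 and 0.050 would be significant to one analyst and not to another. Separately, the trial is powered for a shift across the mRS, yet its efficacy look is triggered by a statistic that discards about a quarter of that information.

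**Working it through.** **Inputs from the SAP.** 188 per group, 90% power, two-sided 0.05, common odds ratio 1.8, six categories (mRS 5 and 6 combined), 6% loss, 400 ideal patients, maximum 500, efficacy look at 300, boundaries 2.834 and 2.004. Section 3 assumes no effect in patients treated outside the target time, and gives 60% as the current rate of meeting that target and 80% as the desired rate.

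**Assumption.** Figure 1 is not shown, so four control distributions (percent in mRS 0, 1, 2, 3, 4, 5-6) were assumed:

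- A: 10, 12, 13, 15, 18, 32
- B: 10, 14, 16, 17, 18, 25
- C: 6, 10, 14, 15, 20, 35
- D: 12, 13, 15, 15, 17, 28

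mRS 0-2 is 35, 40, 30 and 40%. Under an odds ratio of 1.8 it becomes 49.2, 54.5, 43.5 and 54.5%.

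**1. The plan's sample size.** Whitehead: n per group = 6(1.960+1.2816)² / [(ln 1.8)²(1−Σp̄³)], where p̄ are the mean category proportions. With six equal categories Σp̄³ = 0.0278, so n = 63.04/(0.3455 × 0.9722) = 187.7, i.e. 188. A to D give 187.9-190.3. Then 376/0.94 = 400. The plan's figures reproduce.

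**2. The plan's boundaries.** 2.004 × √2 = 2.834, but the two-look O'Brien-Fleming pair at equal information is 2.797/1.977; 2.004 is the three-look constant (simulated 2.003). Also, n=300 is 300/400 = 0.75 or 300/500 = 0.60 of the final sample, not 0.50. Applied to one statistic at both analyses, 2.834/2.004 gives an overall alpha of 4.55% (N=400) or 4.63% (N=500): conservative, but not the named boundary.

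**3. The stated ground.** Standard group-sequential theory needs correlation √(n1/n2) between looks. For the ordinal (tie-corrected rank, i.e. proportional-odds score) statistic, 40,000 simulated trials per setting gave 0.866 for 300/400 (theory 0.866) and 0.772-0.778 for 300/500 (theory 0.775). The usual boundaries therefore apply to it directly.

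**4. Type I error with a binary interim and an ordinal final.** On the same data, with q the proportion at mRS 0-2 and p the control proportions, the correlation of the two statistics is √{[q(1−q)/4] / [(1−Σp³)/12]}. For A: √(0.0569/0.0794) = 0.846; the range is 0.82-0.865. Multiplying by √0.75 or √0.60 gives 0.71-0.75 or 0.63-0.67. The bivariate normal probability of crossing 2.834 at the interim or the final value at the end is:

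| Final ordinal test at | N=400 | N=500 |
|---|---|---|
| 2.004 | 4.65-4.69% | 4.72-4.74% |
| 1.96 | 5.13-5.17% | 5.20-5.22% |

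With 2.004 the total cannot exceed 0.0046 + 0.0451 = 4.97%, whatever the correlation.

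**5. Chance of crossing 2.834 at n=300 (150 per arm).** The binary Z uses the standard pooled variance p̄(1−p̄)(1/nA+1/nB); the printed formula divides by the last bracket where it should multiply.

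- Binary, A: (0.492−0.350)/√(0.421 × 0.579 × 4/300) = 2.49; Φ(2.49−2.834) = 37%.
- Ordinal, A: ln 1.8 × √(300 × (1−0.0345)/12) = 2.89; Φ(2.89−2.834) = 52%. Simulation gives 51%.

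For dilution, the treated distribution is a mixture of shifted and control patients, and the ordinal Z is taken from its expected rank difference:

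| Endovascular patients with the effect | Binary | Ordinal |
|---|---|---|
| 100% | 34-38% | about 51% |
| 80% | 19-21% | 29% |
| 60% | 9% | 13% |

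The dichotomy keeps 73-77% of the ordinal information.

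**6. Final power.** With an odds ratio of 1.8 in all patients, the ordinal test at 2.004 has about 91% power with 400 analysed and 96% with 500 (89% if only 376 are analysed). In scenario A, simulated power of the whole procedure was 90.9% (N=400) with the binary interim and 90.8% with the ordinal interim, so the choice of interim statistic does not move it.

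**The case against.** Several points on the other side are sound.

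- **Type I error.** A reader might infer that the error rate is materially inflated. It is not: the excess is 0.1-0.2 percentage points at worst, and there is none if 2.004 is carried over.
- **The 1.96.** A reader might infer that section 9.1 fixes 1.96. It does not. It gives a confidence level for reporting, in a sentence that follows the description of the secondary adjusted model. The only final critical value anywhere in the SAP is 2.004. The fair statement is that the plan is silent on the value for the ordinal test.
- **Crossing is not automatically rejection.** The boundary subsection says reject and stop, but the DSMB guidance makes crossing the start of a deliberation. If the guidance governs, false-positive early stopping is rarer than computed.
- **Access to the ordinal result.** A reader might infer that the DSMB may see the ordinal result only after a binary crossing. The guidance sets an order of consideration after a crossing; it does not forbid looking otherwise.
- **Stringency may be wanted.** Section 4 calls for stringent, conservative boundaries, and a harder gate fits that aim. But the plan does not offer this as its reason for dichotomising; it says no method exists. Stringency can be set through the boundary value without changing the endpoint.

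What survives is the wrong premise, the unassigned critical value and the less sensitive look.

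**Conclusion.** The point holds in this form. The justification for a binary interim is incorrect, and 2.004 attaches to no final test that section 9.1 names; both follow from the text without assumptions. The type I effect is negligible, but the ambiguity over the decisive test should be closed before unblinding.

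The loss of sensitivity is about 13-17 percentage points if the odds ratio of 1.8 holds in everyone, about 8-10 with 80% ideal patients and about 4 with 60%. These figures rest on the assumed control distributions and, for the last two, on section 3's assumption of no effect in late-treated patients. The loss concerns the chance of stopping early. A reader might infer that the trial itself is underpowered as a result; the calculations do not support that. Dilution would lower final power too, but that is not caused by the choice of interim statistic.

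**What to change.** 1. In section 4, delete the statement that no technique exists. Use the Z from the primary proportional odds model at n=300 and at the final analysis.
2. Do not simply move 2.834/2.004 to that Z. Compute one O'Brien-Fleming boundary at the actual information fraction, preferably by alpha spending because the final size may lie between 400 and 500. The classical form gives about 2.33/2.015 for 300/400 and 2.57/1.99 for 300/500. A spending function gives slightly different values, so name the form used.
3. In section 9.1, state the final critical value for the ordinal test and the matching confidence level: 2.015 corresponds to p = 0.044 and 95.6% limits, 1.99 to p = 0.046 and 95.4% limits. State the corresponding significance level for the Fisher fallback.
4. Give the DSMB mRS 0-2, mortality and the tPA subgroups as supporting data.
5. If the binary trigger is kept, give its real reason and state explicitly that the final ordinal test uses the adjusted final boundary rather than 1.96.

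The cost is wording in the SAP and the DSMB instructions. The data are the same, and the DSMB guidance already calls for the ordinal model at the interim.
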